### Intervention and control

The intervention teams implement an intake intervention consisting of four parts: eHealth modules, Routine Outcome Monitoring, peer support and training of clinicians.

Firstly, eHealth modules are an accessible way for patients to prepare the face to face consultations together with relatives, offer opportunities for patients to participate actively in treatment and support shared decision making [46–48]. Secondly, Routine Outcome Monitoring (ROM) is integral part of the digital intake approach. ROM implies regular measurement of clinical outcomes, at the beginning, during and at the end of treatment, aiming to provide feedback (e.g. with graphics) on the patients' progress during treatment and use the information to adjust treatment [49–52]. At the intake (and later on during treatment), ROM is a useful tool to involve patients in their treatment process by means of providing information by which shared decisions are made about treatment [18, 53]. In this initiative, ROM results visualised in a graphic environment, are presented as 'the recovery trajectory of the patient'. The participating departments all use the same ROM questionnaire which measures symptoms and functioning. Two ROM measurements in the intake process may contribute to meaningful results which are not dependent on a single measurement point. Thirdly, the availability of peers for counselling is a promising approach empowering patients to participate in treatment [54]. Finally, training of clinicians and follow-up training sessions take place to stimulate and facilitate the requested changing roles of clinicians and patients [36] in the new intake approach.

The eHealth modules are designed to explore treatment needs, expectations and preferences of patients. With these modules patients prepare themselves, along with relatives, for the face to face intake consultations, which are intended to lower decisional conflict, stimulate patient participation and facilitate the dialogue between patients and clinicians about choices in treatment. The content of the eHealth modules is described in Table 1.

In Fig. 2 the usual and new digital intake-processes are described. Patients of the intervention group follow the first pre-intake module before the first face to face intake consultation and the second module just after the first and before the second face to face intake consultation. Patients follow the eHealth modules at home on their own device, a computer or tablet. The estimated time for completing each module is 45 min. While filling

**Table 1** Content of intake eHealth modules

First module a pre-intake intervention (before the first intake consultation):

- Patients are informed about psychiatric symptoms and the influence on daily life (e.g. with animations).
- Patients work on questions about their life events, symptoms, the burden and impact of the mental health problems on daily life (before and after the symptoms) and the urgency which problem changing first. Preferably, this preparation takes place together with a relative.
- Routine Outcome Monitoring (ROM) is integral part of the eHealth module.
- Patients and clinicians, who perform intakes, get a summary of the degree of (dis)satisfaction about life domains, burden of symptoms and the recovery line (ROM).
- During participation in the eHealth module, patients get the opportunity to contact with peers (by phone or mail) who can support and prepare them for the intake consult.

Second module between first and second intake consultation:

- Prior to the second face to face consultation, patients look back on the results of the first module and face to face intake consultation. The summary of this first step could be supplemented with new insights. In addition, patients work on questions about the most burdening mental health problem and their own coping style (i.e. type of coping, how to mobilise individual resources). Relatives are asked to answer some of these questions from their perspectives. Finally, the patient starts with preparing their own treatment goals.
- Equal to the first module, contacting peers is also possible while following the second module.
- When the module is completed, patients and clinicians will also get a summary of the answered questions.

out the eHealth modules, patients get the opportunity to have contact with peers (by phone or mail) who can support and prepare them for the intake consult. Peers have life experience with mental illness and treatment. They are already working at GGz Breburg and are experts in supporting patients. They have completed specific education about how to support patients using their experience in mental health care and get also instruction in the way to assist patients who are following eHealth. To prepare for the first consultation, the completed modules are visible for both the patient and the clinician. During this first intake consultation patients and clinicians discuss results of the first pre-intake module by exploring the burden and impact of the mental health problems on daily life. During the second face to face consultation patient and clinician complete, using the results of the second module, the exploration about problems, coping and goals and take shared decisions about the treatment policy and goals. After the second intake consultation the treatment starts. In both conditions the number of face to face contacts in the intake procedure are the same. To make sure that patients and clinicians have sufficient time to discuss the results of the eHealth module, in the new intake approach the first intake consult will take 30 min longer. Because ROM is a promising tool which visualises symptoms severity and functioning, stimulates effective communication between

[figure not shown]

patients and clinicians and empowers patients [49, 53] in the new digital intake approach an additional ROM moment is planned. While the intake as usual includes a single ROM measurement linked to the face to face intake consultation, the new intake approach includes two measurements: one measurement incorporated in the first eHealth module and one, as usual, linked to the face to face intake consultation. In both conditions the multidisciplinary team consultation keeps a role in checking the quality and appropriateness of the proposed treatment and process steps, according to multidisciplinary guidelines.

To stimulate and facilitate the new way of working in the digital intake, the clinicians of the intervention teams follow a training of three half-day sessions in a period of up to four weeks. Aim of this training is gaining insight, knowledge and skills in the application of recovery supported care, shared decision making and eHealth with the purpose to facilitate patients to participate in their intake and treatment process and to stimulate an equivalent interplay between patients and clinicians. During the course of the study at least two follow-up training meetings are organised in the intervention group aimed to discuss clinicians' experiences with the new way of working.

### Study flow

Patients who are referred to one of the participating departments, are invited for an intake consult. Patients

who are planned for an intake consultation with a clinician of the intervention group, are assigned to the intervention team and will get the new eHealth intake automatically. Patients who have this first appointment with a clinician of the control group, are assigned to the control group and will follow the intake as usual. In addition, both groups of patients, who follow the new intake process and the intake as usual, will be invited to participate in the evaluation research consecutively. Research assistants inform all patients (who meet the inclusion criteria) about the research, ask them to participate in the study and obtain written informed consent.

Three measurement points will be scheduled (see Table 2): baseline assessment (T0) and two measurements (T1, T2) after the intake (T1 = two weeks after intake, T2 = two months after intake). Because only T1 and T2 contains additional questionnaires for this research, written informed consent will be asked during the first face to face appointment, just before T1. Patients who give informed consent for the research, are completing self-report questionnaires organised by independent research assistants. In addition to T1, clinicians answer questions about shared decision making regarding their patients. Patients and clinicians who participate in the study, receive a request by email to complete the questionnaires. If necessary, one week later they get a reminder by email. After nine and fourteen days the research assistant calls patients who have not yet

**Table 2** Measurement points

| Assessment/Questionnaire                                                                                                                    | Baseline (T0) | 2 weeks after intake (T1) | 2 months after intake (T2) |
|---------------------------------------------------------------------------------------------------------------------------------------------|---------------|---------------------------|----------------------------|
| Primary Outcome Parameter                                                                                                            |               |                           |                            |
| Decisional Conflict                                                                                                                         |               |                           |                            |
| Decisional Conflict Scale patient                                                                                                           |               | X                         | X                          |
| VAS patient (additional)                                                                                                                    |               | X                         | X                          |
| VAS clinician (additional)                                                                                                                  |               | X                         |                            |
| Secondary Outcome Parameters                                                                                                         |               |                           |                            |
| Patient participation in mental health (treatment).
Patient Participation Questionnaire                                                  |               | X                         | X                          |
| Shared Decision Making process
SDM-Q-9 Patient and clinician.                                                                            |               | X                         | X                          |
| Working alliance
PDRQ-9                                                                                                                  |               | X                         | X                          |
| Adherence to treatment
Drop-out, no-show                                                                                                 |               | EPR                       | EPR                        |
| Symptoms-functioning
SQ-48 (=ROM)                                                                                                        | X             | X                         | X                          |
| Patients' characteristics                                                                                                            |               |                           |                            |
| Patients' characteristics
(sex, age, educational level, diagnosis, SQ-48 score,
previous treatment at GGz Breburg, length of waiting) | EPD           |                           |                            |
| Motivation
Demand for treatment on their own initiative? (1 item)                                                                        | X             |                           |                            |
| Achieving personal treatment goals
(1 item)                                                                                              |               |                           | X                          |

EPR, Electronical Patient Records

completed the questionnaires. Patients who do not use internet, receive paper questionnaires by mail.

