A cluster randomised design at the level of intake-teams and participation of intake-teams in separate multidisciplinary consultations will serve to limit contamination effects between intervention and control groups [45]. The pairs of intake groups within a department are randomly assigned to either the experimental or control condition (matched pairs). The matched teams within each department perform intakes for a similar population of patients in a similar geographic catchment area and have similar personnel. Randomisation of the intake-teams is conducted by an independent researcher, using a syntax in SPSS, which allocates the matched pairs to the control (code 0) or intervention group (code 1). To reduce bias, data collection for this study will be carried out by research assistants, independent of the principal investigator and treatment, with self-report instruments completed by both patients and clinicians. This results are not visible at patient level during intake and treatment. Only the outcome parameters no-show, drop-out and clinical outcome (ROM) will be collected in the context of treatment. As is common practice in cluster randomised RCTs, propensity analyses will be performed at the analytical stage to correct for possible biases in the randomisation process [45].

During inclusion, while informing patients and asking them for written informed consent, the research assistants are blinded for the study arm. The questionnaires

[figure not shown]

Fig. 1 Participating departments and intake teams

are based on self report and hence do not require assessment by a research assistant. Due to the randomisation at the team level and the nature of the intervention, blinding of the clinicians and patients is impossible.

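### Consent is asked only after the intervention arm has been sent the first eHealth module, so the study sample is formed after exposure has begun in one arm only

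*Protocol*

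**What the plan says.** Under Randomisation and blinding, the protocol randomises the two intake teams within each department as a matched pair; patients are not randomised. Study flow explains how a patient reaches an arm. On the intervention side these are the people "who are planned for an intake consultation with a clinician of the intervention group, are assigned to the intervention team". The digital intake then follows without any separate request. On the control side, "Patients who have this first appointment with a clinician of the control group, are assigned to the control group". Who makes the appointment, and by what rule, is not stated.

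Intervention and control gives the order of events: "Patients of the intervention group follow the first pre-intake module before the first face to face intake consultation". That module contains a ROM measurement and offers contact with peers. Control patients have a single ROM measurement, tied to the consultation.

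On consent, Study flow states that "written informed consent will be asked during the first face to face appointment, just before T1". The reason given is that research-specific questionnaires occur only at T1 and T2.

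Three safeguards are described. Both groups are invited consecutively. During inclusion "the research assistants are blinded for the study arm". Propensity analyses are planned to correct for biases in the randomisation process.

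**The concern.** Random allocation of teams protects the comparison only if the patients who end up in the two arms are selected in the same way. Here the intervention arm passes through an extra step before anyone is asked to join: a module of about 45 minutes, done at home. A patient whom that step discourages from attending, or makes less willing to take part in research, disappears before enrolment. Control patients meet no such step.

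If losses differ between arms and those lost differ in decisional conflict, the primary contrast mixes the effect of the intake with a difference in who was enrolled. Secondary outcomes are exposed as well. No-show and early drop-out are the adherence measures, and a no-show at the first consultation falls before consent.

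**Working it through.** **1. Sequence in each arm (Study flow; Intervention and control)**

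| Step | Intervention | Control |
|---|---|---|
| Arm fixed | by clinician booked | by clinician booked |
| Before first consultation | module 1, ROM, optional peer contact | no module |
| First consultation | consent asked | consent asked |
| Afterwards | module 2, second consultation, T1, T2 | second consultation, T1, T2 |

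Consent follows the start of exposure in the left column only. Study flow also places consent just ahead of T1, although T1 is two weeks after an intake of two consultations. On either reading consent comes after module 1.

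**2. What each safeguard reaches**
- Consecutive invitation covers those who attend the first consultation, not those lost before it.
- Blinding of research assistants limits selection by the recruiter. It does not stop patients from selecting themselves, because the protocol says patients cannot be blinded. The Discussion calls the assistants only partly blinded, and Treatment integrity has research assistants register module completion, which reveals the arm.
- Propensity analyses adjust for measured covariates among enrolled patients. In Table 2 the DCS is measured at T1 and T2 only, so baseline imbalance on the primary outcome can be neither checked nor adjusted for. Digital ability is not among the listed characteristics.
- Intention-to-treat starts from enrolled patients. The 10% drop-out in the sample size section is counted among participants, so losses before consent are not covered.

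**3. The plan's own sample size**
Inputs: d = 0.5, alpha 0.05 (taken as two-sided), 65 per arm, ICC 0.01, 10% drop-out.
- Power with 65 per arm: 0.81, against 0.80 stated.
- Design effect with m = 19 per team: 1 + 18 × 0.01 = 1.18; 65 × 1.18 = 76.7, so 77 as stated.
- Drop-out: 77 / 0.9 = 85.6, so 86 against 88 stated. With m = 22, 65 × 1.21 = 78.65, so 79, and 79 / 0.9 = 87.8, so 88.

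The figure of 88 per arm reproduces closely enough and is not in dispute.

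**4. Illustrative size of a shift (assumed inputs)**
The protocol gives no attendance or consent rates. Let q be the excess share of assigned intervention patients lost before consent, and D the difference in mean DCS, in SD, between those lost and those who stay. If stayers have mean S, the mean of all assigned is (1 − q)S + q(S + D) = S + qD. The contrast shifts by q × D.

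Precision: 88 × 0.9 = 79.2 completers per arm, or 19.8 per team; design effect 1 + 18.8 × 0.01 = 1.188; effective n = 79.2 / 1.188 = 66.7; SE = √(2 / 66.7) = 0.173 SD. Type I error at shift b is Φ(b/SE − 1.96) + Φ(−b/SE − 1.96). Power is 0.82 without a shift.

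| q | D | Shift (SD) | Share of d = 0.5 | Type I error | Power if the shift works against the intervention |
|---|---|---|---|---|---|
| 0.05 | 0.25 | 0.013 | 2.5% | 0.051 | 0.80 |
| 0.10 | 0.5 | 0.05 | 10% | 0.060 | 0.74 |
| 0.20 | 0.5 | 0.10 | 20% | 0.089 | 0.64 |
| 0.20 | 0.8 | 0.16 | 32% | 0.152 | 0.50 |

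The definition of D matters. If it compares those lost with the whole arm, the shift is q/(1 − q) × D: 0.10/0.90 × 0.5 = 0.056 SD and 0.20/0.80 × 0.8 = 0.20 SD. A larger sample narrows the interval but leaves the shift in place.

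**The case against.** The strongest reply is that the safeguards are real. Teams in a pair serve similar populations and catchment areas. Research assistants work independently of treatment and approach everyone eligible. The arms will be compared on education, motivation, baseline SQ-48, previous treatment and waiting time. A missed first consultation keeps a patient out in either arm, so only an excess loss in one arm matters, and nothing in the protocol shows one. All of this stands. It lowers the risk and leaves the size open, but it does not change the order of exposure and consent.

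A reader might also infer several stronger points that the document does not support:
- **Planners steer patients without internet to control teams.** The protocol does not say who plans or whether they know the allocation. The provision for paper forms concerns the research questionnaires.
- **Patients who stop at the module never enter.** Completing it is not a condition for the consultation or for inclusion; the degree of completion is only monitored.
- **The T0 motivation item in Table 2 contradicts the consent moment.** It can be read as routine intake data, like the T0 SQ-48.
- **The bias favours the new intake.** That is plausible, but the direction cannot be derived from the text.

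Finally, earlier consent does not produce a DCS score for someone who never attends, since that patient has no intake decision to rate. This is correct and limits what the fix can achieve.

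**Conclusion.** The concern holds as a weakness of design. The protocol's own sequence places enrolment after the start of exposure in the intervention arm only, describes no rule or concealment for the booking that decides the arm, and has no baseline DCS with which to examine the consequence. It does not show that bias will occur. Direction and size are unknown.

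The illustrative shifts of 0.05 SD (10% of the target effect) and 0.16 SD (32%) rest on assumed values of q and D, on D being measured against those who stay, and on the protocol's ICC of 0.01. With little excess loss, or with lost patients who resemble the rest, the shift is negligible. The change is worth making because it is cheap and because intention-to-treat among enrolled patients cannot recover those never enrolled.

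**What to change.** 1. Ask for consent with the intake invitation, before module 1 is issued, in both arms. Define the intention-to-treat population as everyone consented from that point.
2. Assign new referrals to the two teams of a department by a pre-specified rule that planners can neither predict nor influence. Strict alternation would not do, because the next assignment is always known.
3. Keep a log of all eligible referrals per team, with consent status and reason for loss, and report it by arm.
4. Reconcile Randomisation and blinding with the Discussion on whether research assistants are blinded or only partly blinded at inclusion.

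Cost: an amendment of the consent moment, an instruction to those who plan intakes, and the upkeep of a log. Sample size is unchanged by this point. Some consented patients will not attend intake and will lack T1 data, so hidden selection becomes visible missingness and is not fully removed. If inclusion has already started, the planning rule and the log can still be introduced, and earlier referrals might be reconstructed from patient records.

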### Outcome measures

The outcomes of interests will be decisional conflict (primary outcome), patient participation, shared decision making process, working alliance between patient and clinician, adherence to treatment and clinical outcome (secondary outcomes). The outcome measures are visualised in Fig. 3 and the measurement points in Table 2.

The level of decisional conflict is closely related to the secondary outcome parameters patient participation in treatment, shared decision making process and working alliance. Less decisional conflict is associated with more patient participation in decision making about treatment, a better shared decision making process and equality in the working alliance [26, 44, 54].

